### Sample Size and Power

The primary outcome for the proposed trial is successful engagement in care. For those who test seronegative at baseline, we define engagement in care as participation in routine HIV testing. For those who test seropositive at baseline, we define engagement in HIV care as linkage and retention in HIV care (per the Institute of Medicine guidelines of linkage within 30 days of diagnosis and at least 2 physician visits with a CD4 and viral load test in 12 months) and achievement of viral suppression. We define power as correctly identifying the difference in the proportions of YMSM with serospecific engagement in HIV care within 15 months of each active treatment condition (3 arms: SUBI-CTR, SUBI-SUBI, CTR-SUBI) to the control arm (CTR-CTR), thus powering for 3 independent hypothesis tests. Our sample size calculations are based on a 2-sample test of proportions using a 2-sided significance level of *P*<.05 altered by the number of comparisons using a Bonferroni adjustment (significance level is *P*=.02 for 3 comparisons). To have 80% power to compare each active treatment to the control group in a 4-arm trial, we require at least 500 participants to find a 20% difference between each treatment and control and 228 participants to find a 30% difference. To allow for 20% loss to follow-up (our previous trials have each achieved retention rates of >90%), we estimate a sample of 600 YMSMTG to be enrolled.

Participants may continue the study even if they miss follow-ups or visits intermittently over the data collection period. We will compare those who completed different follow-up interviews with those who did not on key predictors from the baseline assessment to check for possible sampling bias due to missing data. Missing data will be minimized by the computer-based entry for all measures. The use of Expectation-Maximization algorithm and multiple imputation approach in longitudinal analyses will help overcome missing data concerns when appropriate.

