### Trial Design

The research activities involve a 4-arm factorial RCT of approximately 600 AOD-using YMSMTG aged 15-29 years in the DMA. We will follow participants for 18 months, with follow-up assessments collected every 3 months.

The intervention comprises 2 visits separated by 3 months. Participants are randomized to receive either CTR (control) or a SUBI-adapted version of CTR (referred to as SUBI; intervention) in each visit. To examine how the sequencing and dosing of interventions impacts efficacy, we randomize at baseline into a factorial RCT. The control arm will receive CTR-only at both study visits 1 and 2. Experimental arm 1 (CTR+SUBI) will receive CTR at visit 1 and SUBI at visit 2. Experimental arm 2 (SUBI+CTR) will receive SUBI at visit 1 and CTR at visit 2. Experimental arm 3 (SUBI+SUBI) will receive the intervention condition at visits 1 and 2. Individuals who test HIV-positive at study visits 1 or 2 will receive case management and linkage to care, as offered routinely by each ASO where study activities take place.

This 4-arm factorial randomized design will help answer 3 important questions: (1) what is the impact of adapting current CTR to include SUBI on HIV engagement in care and sexual- and substance-related risk-taking behaviors among high-risk YMSMTG; (2) what combination of services (CTR-only, CTR+SUBI, SUBI+CTR, SUBI+SUBI) has the greatest impact on engagement in HIV prevention (where engagement in care is defined as routine HIV testing for seronegative YMSMTG and linkage and retention in care for seropositive YMSMTG); and (3) if effective, what are the costs of delivering SUBI compared with those of delivering CTR?

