9	Focus on repeat HIV testing	Cost and benefit analysis of testing	Focus on linkage to HIV care	Cost and benefit analysis of testing
10	PrEP referral	Interpretation of HIV test results	Links to Component 1 (goals, strengths, and substance use as a barrier)	Interpretation of HIV test results
11	Links to Component 1 (goals, strengths, and substance use as a barrier)	Reinforce plan for reducing risk based on test results	Summary and plan for action	Renegotiate risk reduction plan
12	Summary and plan for action	—	—	Discuss disclosure, partner services, appropriate referrals for medical evaluations, and early intervention services
13	—	—	—	Collect specimen for confirmatory testing^d^

^a^SUBI: substance use brief intervention.

^b^PrEP: pre-exposure prophylaxis.

^c^CTR: counseling, testing, and referral.

^d^Each ASO has specific procedure for confirmatory testing. Detroit-Blood draw for confirmatory testing: results in 3 days. Ypsilanti-Rapid test for confirmatory testing: results in 1 min. Flint-Rapid test for confirmatory testing: results in 20 min.

With permission, counselors begin to discuss the importance of linkage to HIV care in Step 9. Counselors explain how people with HIV can live healthy lives provided that they attend medical appointments and take medications while also exploring the participant’s perceived benefits of seeing a HIV medical provider.

Step 10 links the strengths and goals from Component 1 as a tool to continue to encourage linkage to care. Possible barriers to linkage to care are explored, with an emphasis on the potential impact of substance use.

Step 11 reflects on the participants’ goals for next steps toward linkage to care with an emphasis on eliciting goal-setting with goals that are achievable, clear, and have a defined end point. Counselors provide support to participants by affirming their strengths to meet these goals. Counselors thank the participants for their time and end the session.

#### Substance Use Brief Intervention at Study Visit 2

For those who received a nonreactive HIV test result at visit 1 and who are randomized to receive SUBI at study visit 2, the same intervention components and steps are delivered, as described above. For those who received a reactive test result at visit 1, the SUBI session focuses employing MI skills to address adherence with HIV care and the role of substance use.

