### Statistical Analysis

Descriptive statistics of the clinical and demographic characteristics of the participants will described for all and by treatment group. These will be compared between treatment groups using *t* tests or Wilcoxon rank sum tests for continuous variables and chi-square tests for categorical variables. We will conduct primary analyses of our pooled successful engagement measure using logistic regression analyses to compare each active treatment group with the control in pairwise comparison tests at an adjusted significance level of .017 to reduce Type-I errors in our 4-arm trial. We will then conduct exploratory logistic regression analyses by sero-status. For seronegative YMSMTG, the proportion of participants who obtain at least 2 tests at least 3 months apart within 15 months will be calculated and presented with corresponding 95% exact binomial CIs. Among seropositive YMSMTG, we will examine how intervention conditions influence HIV linkage and retention in care per IOM guidelines. We will also examine for all participants the pursuit of substance use treatment services (if necessary). Hence, for seronegative participants, the outcome will be repeat HIV testing at regular intervals, and for seropositive participants, the outcome will be linkage and retention in care. We will not consider viral suppression in the regression analysis due to the short time period available to achieve suppression. However, we will present descriptive statistics on viral load and suppression across the 4 treatment arms. The regression will be run with group assignment in the model while controlling for patient, structural, and agency characteristics. Interactions between group assignment and these characteristics will be tested to explore potential moderators of treatment effect. We will repeat these analyses for STI/ATOD biomarkers conducted during the trial. Additional analyses include comparing groups in (1) the average number of tests obtained using Poisson regression and (2) time to getting tested using repeated events survival analysis.

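### For participants diagnosed at baseline, 30-day linkage is settled about two months before session 2, so it is better compared by visit-1 session than across four arms

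*Protocol article*

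**What the plan says.** Sample Size and Power limits the seropositive definition to baseline diagnoses: "For those who test seropositive at baseline, we define engagement in HIV care as linkage and retention in HIV care". The standard is "linkage within 30 days of diagnosis and at least 2 physician visits with a CD4 and viral load test in 12 months".

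Trial Design fixes the timing and content of the sessions: "The intervention comprises 2 visits separated by 3 months". On the arms: "The control arm will receive CTR-only at both study visits 1 and 2", and "Experimental arm 1 (CTR+SUBI) will receive CTR at visit 1 and SUBI at visit 2". The other two arms both receive SUBI at visit 1.

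The Intervention section, on SUBI at study visit 2, says: "For those who received a reactive test result at visit 1, the SUBI session focuses employing MI skills to address adherence with HIV care". The SUBI content that promotes linkage (Table 2, Component 2b) is delivered at the visit where the reactive result is given.

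Statistical Analysis uses logistic regression on the pooled engagement measure to "compare each active treatment group with the control in pairwise comparison tests at an adjusted significance level of .017". Under exploratory analyses by serostatus it then adds: "Among seropositive YMSMTG, we will examine how intervention conditions influence HIV linkage and retention in care per IOM guidelines". It names linkage and retention together as the seropositive outcome. The article does not mention that two pairs of arms are identical during the linkage window.

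**The concern.** A treatment can affect an outcome only if it is given before the outcome is settled. For a baseline diagnosis, SUBI at visit 2 comes after 30-day linkage has already happened or failed. Examined by arm, linkage then has two weaknesses:

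- **Interpretation.** CTR+SUBI counts as an active arm although none of its participants has received SUBI when linkage is settled. A difference near zero could be taken as evidence that SUBI does not help linkage, and a chance difference as evidence that it does. Neither says anything about SUBI.
- **Precision.** The one informative linkage contrast is SUBI versus CTR at visit 1. Arm by arm, it is estimated twice, each time from one arm per side, although two arms per side are available. The seropositive group is probably small, since entrants report unknown or negative status.

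**Working it through.** **The plan's sample size.** With the pooled-variance two-proportion formula, two-sided alpha 0.05/3 and 80% power, an assumed control rate of 0.30 gives 125 per arm for 0.30 versus 0.50 and 57 per arm for 0.30 versus 0.60. Then 4 × 125 = 500 and 4 × 57 = 228, as printed. The control rate is not stated. These figures concern the pooled outcome and do not turn on the linkage question.

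**Timing.** The linkage window is 30 days from diagnosis (Sample Size and Power). Session 2 is 3 months after session 1 (Trial Design), or 3 × 30.44 ≈ 91 days. The gap is 91 − 30 = 61 days. If diagnosis is dated from the slowest confirmatory result in the Table 2 footnote (3 days), the gap is 91 − 33 = 58 days. The conclusion is the same.

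**Exposure of a baseline diagnosis, by arm**

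| Arm | Received by day 30 | Received at about day 91 |
|---|---|---|
| CTR+CTR | CTR | CTR |
| CTR+SUBI | CTR | SUBI |
| SUBI+CTR | SUBI | CTR |
| SUBI+SUBI | SUBI | SUBI |

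On 30-day linkage, and assuming that knowledge of a future session has no effect, CTR+SUBI minus CTR+CTR is 0 and SUBI+SUBI minus SUBI+CTR is 0. Only SUBI versus CTR at visit 1 can be non-zero.

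**Precision.** Pooling in pairs doubles each group, so the standard error is multiplied by 1/√2 = 0.707, a cut of about 29% at any sample size. In absolute terms the 95% half-width is 1.96 × √(2p(1−p)/n), with n = N/4 for single arms and N/2 for pooled pairs. The linkage rate p = 0.6 and the total number of baseline seropositives N are assumptions.

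| Assumed N | Single arms | Pooled pairs |
|---|---|---|
| 12 | 78 points | 55 points |
| 30 | 50 points | 35 points |
| 60 | 35 points | 25 points |

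**Joint outcome.** If engagement needs both linkage (probability L) and retention, and visit-2 SUBI raises retention among those linked by r, the CTR+SUBI versus control difference is L × r. With r assumed at 20 points, L = 50%, 70% or 90% gives 10, 14 or 18 points. The effect is attenuated, not removed.

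**Pooled primary, CTR+SUBI versus control.** Assume 0.40 versus 0.60 in seronegatives, 125 per arm and alpha 0.0167. Power with no seropositives is 78.4%; it is below 80% because this pair of rates needs 520 in total. With a seropositive share s and L = 70%, the pooled difference is (1 − s) × 0.20 + s × 0.14, for example 0.197 at s = 5%.

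| Assumed share s | Power, linkage gate only | Power if the whole seropositive effect were zero |
|---|---|---|
| 1% | 78.1% | 77.4% |
| 3% | 77.5% | 75.4% |
| 5% | 76.9% | 73.3% |
| 10% | 75.4% | 67.7% |

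The last column is a bound that the documents do not support, because retention remains open to visit-2 SUBI.

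**The case against.** The strongest case against is that the plan does not commit to a separate arm-by-arm test of linkage. The pairwise tests at .017 attach to the pooled engagement measure. The seropositive analysis is exploratory, its outcome is linkage and retention jointly, and the word condition is used elsewhere in the article for session type as well as for arm. A factorial design makes grouping by session natural, and how an exploratory model is parameterised can be left to the analysis plan. Sequencing is also something the trial sets out to study: a sequence that withholds SUBI until visit 2 does miss the linkage window, and an as-randomised comparison reports that correctly.

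Most of this stands, and it limits the point. A reader might infer that CTR+SUBI is an untreated copy of control throughout, that the four-arm comparison is invalid, or that the trial's second question cannot be answered. The documents support none of these. The arms differ from visit 2 onward, the visit-2 SUBI is aimed at adherence with care, retention runs for 12 months, and the second question also covers routine testing in seronegatives.

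The objection does not remove the narrower point. The text names linkage as something to be examined by intervention condition. If that is done by arm, one contrast carries no information about SUBI and the others use half the data. Nothing in the article steers the analyst or the reader away from this.

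**Conclusion.** The point holds for the 30-day linkage component in participants seropositive at baseline. There, one of three active-versus-control contrasts is zero by design and the other two estimate the same quantity. Pooling by visit-1 session lowers the standard error by about 29%. The timing argument rests only on stated figures and on the absence of anticipation effects.

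It does not hold for the joint outcome, which is attenuated for CTR+SUBI rather than null, and it does not threaten the primary analysis or its sample size. An as-randomised four-arm linkage table is inefficient and easily misread, not wrong.

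Severity is minor. The analysis is exploratory, the documents give no number of seropositives, and the half-widths, attenuation and power figures above all rest on assumed counts and rates. Even pooled, the estimate would probably remain descriptive.

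**What to change.** In the exploratory seropositive analysis in Statistical Analysis, state that 30-day linkage among baseline diagnoses is reported by visit-1 session: SUBI+CTR and SUBI+SUBI pooled, against CTR+CTR and CTR+SUBI pooled. Visit-1 session is itself randomised and infection at baseline precedes it, so the comparison keeps the protection of randomisation.

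Keep the four-arm comparison for 12-month retention and for the joint outcome. Add a sentence that a CTR+SUBI versus control difference in 30-day linkage is not to be interpreted as evidence about SUBI.

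A parallel analysis of visit-2 diagnoses is not recommended. The seropositive definition covers baseline diagnoses only, and a group defined at visit 2 is selected after randomisation by attendance and by infection since visit 1.

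The cost is a change of wording, with no new data and no new participants.

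### The 600 to be enrolled covers 16.7% loss from the required 500, not the 20% stated; at 20% loss, power is about 78% under an assumed 30% control rate

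*Protocol article*

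**What the plan says.** The Sample Size and Power section plans three comparisons, each active arm against CTR-CTR, by a two-sided two-sample test of proportions with Bonferroni adjustment. For 80% power it states "we require at least 500 participants to find a 20% difference between each treatment and control", and 228 for a 30% difference. Enrolment is then set: "To allow for 20% loss to follow-up (our previous trials have each achieved retention rates of >90%), we estimate a sample of 600 YMSMTG".

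The adjusted level is printed in the same section as "using a Bonferroni adjustment (significance level is *P*=.02 for 3 comparisons". The Statistical Analysis section specifies the pairwise tests "at an adjusted significance level of .017 to reduce Type-I errors in our 4-arm trial". The Randomization section gives 1:1:1:1 allocation, so 500 is 125 per arm and 228 is 57 per arm. The control-arm engagement rate behind these figures is not given.

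**The concern.** The minimum of 500, the 20% loss and the enrolment of 600 stand within two sentences of each other and cannot all be true. An allowance for loss divides the required number by the fraction expected to remain; here the required number appears to have been multiplied by one plus the loss. If the full planned loss occurred, the primary comparisons would run below the article's own minimum, on the outcome for which the trial is powered. The two printed alpha levels also call for a check on whether the sample size was computed at the level used for testing.

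**Working it through.** **Inputs from the article.** Family-wise alpha .05, two-sided; 3 comparisons; power 80% per comparison; 500 (125 per arm) for 20 points; 228 (57 per arm) for 30 points; four equal arms; loss 20%; enrolment 600.

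**Assumption.** Control rate 30%, chosen because it reproduces the article's figures; 20% to 60% is examined as a range. A "20% difference" is read as 20 percentage points.

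**Step 1. Reproduce 500 and 228.** With p̄ the mean of the two rates, the pooled-variance formula without continuity correction is

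n per arm = [z(1−α/2)·√(2p̄(1−p̄)) + z(power)·√(p1(1−p1) + p2(1−p2))]² / (p1−p2)²

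At α = .05/3 = .01667, z(1−α/2) = 2.394 and z(power) = 0.842.

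- 30% vs 50%: n = 124.3, rounded up to 125; × 4 = 500.
- 30% vs 60%: n = 56.2, rounded up to 57; × 4 = 228.

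Both match exactly. With α = .017 both match exactly at a control rate of 31%. With α = .02 no control rate from 1% to 69%, on a 1-point grid, gives both figures exactly. At 30% control, for example, .02 gives 120 and 54 per arm, that is 480 and 216. The sample size was therefore evidently computed at .05/3, and .02 is that value to two decimals.

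**Step 2. Allowance for loss.**

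- Remaining after 20% loss: 600 × 0.80 = 480, or 120 per arm; 500 − 480 = 20 short.
- Enrolment needed to keep 500: 500/0.80 = 625.
- Origin of 600: 500 × 1.20 = 600.
- Loss that 600 covers: 1 − 500/600 = 16.7%.

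This step needs no assumption.

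**Step 3. Power for a 20-point difference at α = .05/3.** The formula inverted is

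power = Φ{[|p1−p2|·√n − z(1−α/2)·√(2p̄(1−p̄))] / √(p1(1−p1) + p2(1−p2))}

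At 120 per arm (20% loss):

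| Control rate | Power |
|---|---|
| 20% | 84.4% |
| 25% | 80.9% |
| 30% | 78.4% |
| 35% | 76.9% |
| 40% | 76.4% |
| 50% | 78.4% |
| 60% | 84.4% |

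At 30% vs 50% with other losses:

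- 16.7% loss, 500 remaining, 125 per arm: 80.3%.
- 10% loss, 600 × 0.90 = 540 remaining, 135 per arm: 83.7%.

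**Step 4. The optional alternative.** In 300,000 simulated four-arm trials with a shared control arm, 120 per arm and 30% vs 50%, Holm's step-down procedure raised per-comparison power from 78% under flat Bonferroni to 85% when all three active arms work, and to 81% when two do. With no arm effective, family-wise error was about 4.5% for both.

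**The case against.** **The loss will probably be smaller than 20%.** The article cites retention above 90% in the investigators' earlier trials. At 10% loss 540 remain and power is 83.7% at the reproducing control rate, and any loss up to 16.7% leaves at least 500. This stands as a limit on the consequence. It does not rescue the sentence: 20% is the stated planning allowance, and 600 does not meet it.

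**The power shortfall depends on a rate that the article does not give.** This also stands. At 120 per arm power still exceeds 80% at control rates of 20%, 25% and 60%, and falls below it from 30% through 50%. A reader might infer that the trial is underpowered; the document supports only a small shortfall, over part of the range, at full loss. A condensed article may leave the control rate to the full protocol, so its absence is not an error.

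**The two alpha levels.** A reader might infer that .02 against .017 costs power, or that the trial would test three hypotheses at .02, summing to .06. Neither is supported. The sample sizes reproduce at .05/3, and the only testing rule, in the Statistical Analysis section, is .017. The printed .02 can still mislead: with it, 30% vs 50% needs exactly 480, and a reader checking the allowance would wrongly find 600 sufficient after 20% loss.

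**The word "independent".** The article describes the design as "thus powering for 3 independent hypothesis tests", although the three comparisons share one control arm. A reader might infer that the multiplicity control fails. It does not: Bonferroni is valid under any dependence, so the word affects neither validity nor sample size.

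**Conclusion.** The concern holds for the loss allowance. Enrolment of 600 covers 16.7% loss from 500, and the article's stated 20% would need 625. That conclusion rests on the article's own numbers alone. The consequence is minor: with the assumed 30% control rate, power at the full 20% loss is 78.4%, which is 1.6 points below the stated 80%. The lowest value over control rates of 20% to 60% is 76.4%, at 40%. With loss at or below 16.7%, the article's minimum of 500 is kept and its planned 80% is met, on the same 30% assumption. The printed .02 is a rounding of .0167 that should be corrected for consistency; it is not a cause of lost power.

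**What to change.** Keep 600 and restate the sentence in one of two ways: 600 allows for 16.7% loss from the required 500; or 20% loss leaves 480 participants (120 per arm), with about 78% power for a 20-point difference, naming the control rate on which that rests. The sponsor should use its own planning rate there; 30% is only a back-calculation. Print the Bonferroni level in Sample Size and Power as .017, to match Statistical Analysis. Both are wording changes: they alter neither enrolment nor the analysis, and the stated power or allowance becomes slightly less favourable.

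Optional, and not the correction of an error: Holm's step-down procedure in place of flat Bonferroni. It controls the same family-wise error and raises per-comparison power when more than one arm is effective. It needs no extra participants, but it changes the prespecified primary testing rule. The Results section reports 142 participants already randomized, so it would have to be made as a documented amendment, without reference to outcome data by arm.

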### Randomization

Participants will be randomly assigned to 1 of the 4 conditions using a 1:1:1:1 treatment allocation. The treatment assignments will be generated with the use of a pseudo-random-number generator with permutated blocks that will be used to ensure balance between the numbers of YMSMTG assigned to each treatment. Assignments to the control or intervention arms will use concealment of allocation techniques designed to minimize assignment bias including generating, in advance, the sequence of assignment in sealed envelopes, which will be opened by the counselor at the time of randomization. When YMSM are randomized to receive CTR-only at a visit, they will receive standard CTR (30 min). YMSM randomized to SUBI at a study visit will receive the CTR that has been adapted to include the SUBI. On average, both conditions will last approximately 30 min.

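### A target of 600 covers a 16.7% loss, not the stated 20%: at 20% loss 480 remain, below the plan's own minimum of 500 for 80% power

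*Protocol article*

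**What the plan says.** The relevant text is in the Sample Size and Power section of the protocol article. The primary outcome is successful engagement in care within 15 months, and each of three active arms is compared with the CTR-CTR control. The method is given as follows: "Our sample size calculations are based on a 2-sample test of proportions using a 2-sided significance level of" .05, with a Bonferroni adjustment for three comparisons ("significance level is *P*=.02 for 3 comparisons"). The Statistical Analysis section gives the same adjusted level to three decimals: "pairwise comparison tests at an adjusted significance level of .017".

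The power target is introduced with "To have 80% power to compare each active treatment to the control group in a 4-arm trial", and the requirement follows: "we require at least 500 participants to find a 20% difference between each treatment and control", and "228 participants to find a 30% difference". The Randomization section fixes equal arms ("randomly assigned to 1 of the 4 conditions using a 1:1:1:1 treatment allocation"), so 500 means 125 per arm.

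The next sentence turns the requirement into an enrolment target: "To allow for 20% loss to follow-up (our previous trials have each achieved retention rates of >90%), we estimate a sample of 600 YMSMTG". The article gives no other inflation rule and does not say that fewer than 500 evaluable participants would be enough.

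**The concern.** An allowance for loss should leave the required number after the loss has occurred, so the requirement is divided by the retained fraction. Here the requirement appears to have been multiplied by one plus the loss fraction, which always gives too small a number.

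The figure affects all three primary comparisons. If the trial loses the share of participants it says it has allowed for, each comparison rests on about 120 per arm instead of 125, and the stated 80% power no longer follows from the design. The margin for attrition is also overstated: a team watching retention against a 20% ceiling would believe the design intact when it had already fallen below its own minimum.

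**Working it through.** **Inputs**

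| Input | Value | Source |
|---|---|---|
| Test | two-sample test of proportions, two-sided | Sample Size and Power |
| Level per comparison | .05/3 = .0167 (printed as .02) | Sample Size and Power |
| Level in the analysis | .017 | Statistical Analysis |
| Power | 80% per comparison | Sample Size and Power |
| Required total, 20-point difference | 500 (125 per arm) | Sample Size and Power |
| Required total, 30-point difference | 228 (57 per arm) | Sample Size and Power |
| Allocation | 1:1:1:1 | Randomization |
| Loss allowed for | 20% | Sample Size and Power |
| Enrolment target | 600 | Sample Size and Power |
| Control proportion | not given; 30% assumed | inferred in step 1 |

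**Step 1. Reproduce 500 and 228.** The pooled-variance formula without continuity correction is

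n per arm = [z(1−α/2) × √(2p̄(1−p̄)) + z(1−β) × √(p1(1−p1) + p2(1−p2))]² / (p2 − p1)²

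with α = .05/3, so z(1−α/2) = 2.394, and z(1−β) = 0.8416.

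- 30% vs 50%: p̄ = 0.40. The numerator is [2.394 × √0.48 + 0.8416 × √0.46]² = [1.659 + 0.571]² ≈ 4.970. Dividing by 0.04 gives 124.3, so 125 per arm, **500** in total.
- 30% vs 60%: p̄ = 0.45. The numerator is [2.394 × √0.495 + 0.8416 × √0.45]² = [1.684 + 0.565]² ≈ 5.057. Dividing by 0.09 gives 56.2, so 57 per arm, **228** in total.

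Both printed totals come out exactly. The requirement of 500 is therefore sound on these inputs, and the problem lies only in the step from 500 to 600.

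**Step 2. Check the step from 500 to 600.**

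- Division by the retained fraction: 500 / (1 − 0.20) = **625**.
- Multiplication by one plus the loss: 500 × 1.20 = **600**, the printed figure.
- What 600 leaves after 20% loss: 600 × 0.80 = **480**, or 120 per arm. This is 20 fewer than 500, or 4%.
- Largest loss at which 600 still leaves 500: 1 − 500/600 = **16.7%**.

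**Step 3. Power at the number that remains.** Solving the same formula for power:

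Power = Φ{[(p2 − p1)√n − z(1−α/2)√(2p̄(1−p̄))] / √(p1(1−p1) + p2(1−p2))}

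For 30% vs 50% at α = .05/3:

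| Evaluable total | Per arm | Situation | Power |
|---|---|---|---|
| 500 | 125 | stated minimum | 80.3% |
| 480 | 120 | 600 enrolled, 20% loss | 78.4% |
| 540 | 135 | 600 enrolled, 10% loss | 83.7% |

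The 480 row in full: (0.2 × √120 − 1.659) / 0.678 = (2.191 − 1.659) / 0.678 ≈ 0.785, and Φ(0.785) ≈ 0.784.

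**Step 4. Does the printed level of .02 change the answer?** With .02 taken literally and the same pooled formula, 30% vs 50% needs 480, and 480 gives 80.3% power. But the printed minimum would then be 480, and the 30-point total would be 216, not 228. With .02 and 40% vs 60%, 500 is reproduced, but the 30-point total is again 216, and power at 480 is 78.5%. None of the control proportions tried at .02 (10% to 60%) gives both printed totals. The figure .02 reads as .0167 rounded, in line with the .017 in the Statistical Analysis section.

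**The case against.** The strongest reply is that 20% is a cautious ceiling and not a forecast. The same sentence reports retention above 90% in the team's earlier trials. At 10% loss 540 remain, the minimum is met with room to spare, and power is about 83.7%. This stands as a reason to expect little practical harm. It does not make the sentence true: the plan chose 20% as its allowance and says 600 meets it, yet the minimum is missed for any loss above 16.7%.

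A second reply is that the effect is tiny: 78.4% against 80%, with nothing changed in the comparisons, the error control or the conduct of the trial. That is correct and limits the weight of the point.

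A third is that the power figure depends on an unstated control proportion. This is also correct. At .05/3, 480 participants give 80.9% power if the control proportion is 25% and 84.4% if it is 20%. Those inputs, however, do not lead to the printed 500; they need 472 and 436. The shortfall of 480 against 500 does not depend on any of this.

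A fourth is that loss to follow-up is not the same as a missing primary outcome. Participants may stay in the study after missed visits, and repeat testing is assessed at each follow-up, so some who leave late may already have met the definition. Imputation is also mentioned for the longitudinal analyses. Both soften the consequence, but the article offers neither as a reason why fewer than 500 would be enough.

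**Conclusion.** The point holds. The enrolment target does not provide the allowance claimed for it: 600 covers up to 16.7% loss, while 20% loss leaves 480 against a stated minimum of 500. This follows from the printed numbers alone.

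The error is small: 20 evaluable participants, equivalent to 25 enrolled (625 − 600). At the full 20% loss, power per primary comparison is about 78.4% for 30% vs 50%. That value rests on the assumed 30% control proportion, a two-sided level of .05/3, pooled variance and equal arms, the combination that reproduces both printed totals. It does not threaten the validity of the trial, but it is a wrong figure in the primary power statement and should be corrected.

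**What to change.** Correct the one sentence in Sample Size and Power, in either of two ways:

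1. Keep 600 and state that it preserves the 500 minimum for losses of up to 16.7%, adding if wished that the retention seen in earlier trials would leave about 540.
2. Keep 600 and the 20% allowance, and state that 480 evaluable participants (120 per arm) would then give about 78% power per comparison at the .0167 level. The team should recompute this with the control proportion it actually used, since 30% is inferred here.

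If the team instead wants 80% power to survive a 20% loss, the target becomes 625, that is 25 more. The Results section reports recruitment still under way with 142 randomized, so that option was open when the article was written, but it is not needed to put the text right.

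The two wording options cost one sentence and a slightly less favourable figure. They change nothing in enrolment, conduct or analysis.
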